|-------------------------------|----|------------------------------------------------------------------------------------------------------------------------------------------------------------------------------------------------------------------------------------------------------------------------------------------------------------------------------------------------------------------------------------------------------------------------------------------------------------------------------------------------------------------------------------------------------------------------------------------------------------------------------------------------------------------------------------------------------------------------------------------------------------------------------------------------------------------------------------------------------------------------------------------------------------------------------------------------------------------------------------------------------------------------------------------------------------------------------------------------------------------------------------------------------------------------------------------------------------------------------------------------------------------------------------------------------------------------------------------------------------------------------------------------------------------------------------------------------------------------------------------------------------------------------------------------------------------------------------------------------------------------------------------------------------------------------------------------------------------------------------------------|
|                               |    | 
 
○ None of the investigators receive financial compensation beyond their institutional roles related to this research.
 
 
3. Competing Interests:
 
 
○ The external collaborator responsible for randomization, [name], is a professor affiliated with the Universidad Católica de Santiago de Guayaquil and provides voluntary support to this study. While she is associated with the institution, her role is limited to conducting the randomization process remotely from Miami, USA, ensuring she remains independent from other aspects of the study.
 
○ No other professional or personal affiliations could influence the objectivity of the investigators.
 
                                                                                                                                                                                                                                                                                                                                                                                                                                                                                                                                                                                                                                                                                                                                                                                                                                                                                                                                         |
| Access to data                | 29 | 
Access to Data
 
Access to the full dataset will be restricted to the principal investigator and the designated members of the research team. This ensures the confidentiality of participant information and maintains the integrity of the data throughout the study.
 
1. Data Access Policy:
 
 
○ Only authorized members of the research team will have access to the complete dataset during the study.
 
○ Access will require authentication via secure login credentials to the cloud-based storage system.
 
○ Each team member will sign a confidentiality agreement outlining their responsibilities for data handling and protection.
 
 
2. Conditions for External Access:
 
 
○ Requests for access to anonymized data for secondary analysis or replication studies will be considered only after the study's primary results have been published.
 
○ External access will require approval from the principal investigator and the Ethics Committee of the Instituto Superior Universitario "Portoviejo."
 
○ All shared data will be anonymized to ensure that no identifying information about participants is disclosed.
 
 
3. Long-Term Data Access:
 
 
○ An anonymized version of the dataset will be archived securely for five years after the study's completion, in compliance with institutional and international research guidelines.
 
○ After this period, the dataset will be permanently deleted unless additional ethical approvals are obtained for its continued use.
 
 |
| Ancillary and post-trial care | 30 | 
Ancillary and Post-Trial Care
 
Given the non-invasive and low-risk nature of the intervention (kissing), no ancillary or post-trial care is anticipated to be necessary for participants. However, the following provisions are in place to address any unexpected concerns:
 
 
1. Post-Trial Contact Information: Participants will receive the contact details of the principal investigator, who will be available to address any questions or concerns following their participation in the study.
 
2. Access to Medical Care: Should any participant experience discomfort or a perceived adverse effect related to the study, they will have access to the medical facilities of the Universidad Católica de Santiago de Guayaquil, where the study is conducted. The university's medical staff will provide free consultation and basic treatment if necessary.
 
                                                                                                                                                                                                                                                                                                                                                                                                                                                                                                                                                                                                                                                                                                                                                                        |

|                             |     |                                                                                                                                                                                                                                                                                                                                                                                                                                                                                                                                                                                                                                                                                                                                 |
|-----------------------------|-----|---------------------------------------------------------------------------------------------------------------------------------------------------------------------------------------------------------------------------------------------------------------------------------------------------------------------------------------------------------------------------------------------------------------------------------------------------------------------------------------------------------------------------------------------------------------------------------------------------------------------------------------------------------------------------------------------------------------------------------|
|                             |     | 3. Post-Trial Feedback: Participants will have the opportunity to request a summary of the study's results once the analysis is complete. This ensures transparency and acknowledges their contribution to the research.                                                                                                                                                                                                                                                                                                                                                                                                                                                                                                 |
| Dissemination policy        | 31a | Plans for Disseminating Study Results 
 
○ The findings of this study will be disseminated through publication in a peer-reviewed journal of high impact in the fields of dentistry and public health.
 
○ Results will also be presented at national and international conferences to share insights with the broader scientific community.
 
                                                                                                                                                                                                                                                                                                                       |
|                             | 31b | Authorship Eligibility Guidelines and Any Intended Use of Professional Writers 
 
○ Authorship will be determined based on the guidelines of the International Committee of Medical Journal Editors (ICMJE), ensuring that all contributors who meet the criteria for authorship are included.
 
○ No professional writers will be used in the preparation of manuscripts. The research team, led by the principal investigator, will take full responsibility for drafting and revising all study-related publications.
 
                                                                                                                                           |
|                             | 31c | Plans, if Any, for Granting Public Access to the Full Protocol, Participant-Level Dataset, and Statistical Code 
 
○ An anonymized version of the dataset will be made publicly available in an appropriate research data repository after publication, in line with open science principles and journal requirements.
 
○ Results and updates will also be added to the ClinicalTrials.gov registry under the identifier NCT06501729 to ensure transparency and accessibility.
 
○ The full protocol and statistical code will be shared upon reasonable request to the principal investigator, subject to approval by the institutional ethics committee.
 
 |
| Inform ed consent materials | 32  | Appendices 1                                                                                                                                                                                                                                                                                                                                                                                                                                                                                                                                                                                                                                                                                                             |
| Biologic al specimens       | 33  | Appendices 2                                                                                                                                                                                                                                                                                                                                                                                                                                                                                                                                                                                                                                                                                                             |

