| Study setting                                             | 9  | 
The study will be conducted at the dental clinics of the Universidad Católica de Santiago de Guayaquil. These facilities provide a controlled and sanitized environment, adhering to strict biosecurity protocols. Data collection will take place two days per week, during which the space will be reserved exclusively for the study.
 
The following arrangements have been made to ensure participant comfort and privacy:
 
 
○ Oral Health Assessments: Dental chairs within the clinic will be used to evaluate the oral health of participants prior to the intervention.
 
○ Privacy During Interventions: Private spaces separated by screens (biombos) will be set up to allow participants to kiss in a comfortable and discreet environment.
 
○ Saliva Sample Collection: Saliva samples will be collected and pH measurements will be performed in the same private setting immediately following the intervention.
 
 
This controlled environment is designed to ensure participant safety, facilitate standardized data collection, and maintain the integrity of the study.
 |
| Eligibility criteria                                      | 10 | 
Inclusion Criteria:
 
Participants must meet the following criteria to be eligible for the study:
 
 
1. Be between 18 and 28 years old.
 
2. Have good oral health, defined as a CPO index <math>\leq 3</math>, according to the criteria of the World Health Organization.
 
3. Be in a romantic relationship with a partner willing to participate in the study.
 
4. Have sufficient availability to attend all study appointments.
 
 
Exclusion Criteria:
 
Participants will be excluded from the study if they meet any of the following conditions:
 
 
1. Presence of systemic diseases that could alter salivary pH (e.g., diabetes, autoimmune disorders).
 
2. Use of medications that may affect salivary pH, including: 
 
○ Antidepressants (tricyclics): e.g., amitriptyline.
 
○ Antihistamines: e.g., diphenhydramine.
 
○ Beta blockers: e.g., propranolol.
 
○ Diuretics: e.g., hydrochlorothiazide.
 
 
 
     |

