| Interventions | 11a | 
Experimental Groups (Intervention):
Participants in the experimental groups will engage in a French kiss, defined as a passionate kiss involving the exchange of salivary fluids through the mutual introduction of tongues into each other's mouths, along with lip contact. Participants will receive instructions to perform this kiss for a duration of 40 seconds. While this duration is arbitrary and will be acknowledged as a limitation in the protocol, no prior studies provide a guideline for the specific duration of this type of kiss.
 
 
○ Setting: The intervention will take place in a private space within the dental clinic of the Universidad Católica de Santiago de Guayaquil. Each cubicle, equipped with a dental chair, will be enclosed with screens to ensure the privacy of participants. After completing the kiss, participants will leave the cubicle to provide an unstimulated saliva sample, which will be analyzed to measure pH.
 
 
Control Group:
Participants in the control group will not kiss but will still be required to bring their partners to ensure comparable conditions. The individual who consumes the acidic beverage will remain in the same cubicle for 40 minutes, providing unstimulated saliva samples every 5 minutes, as is required for the experimental groups. The control participants will remain seated and follow the same sample collection timeline as the intervention groups.
 
Implementation Standards:
 
 
○ The intervention (kissing) will be self-administered by participants. The research team will observe the initiation of the kiss to ensure it begins appropriately and will then start the timer
 
 |

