|  |     | 
for the 40-second duration. Once the timer concludes, participants will be asked to leave the cubicle and provide their saliva sample.
 
 
○ Tools and Equipment: 
 
○ Screens (biombos) to provide privacy.
 
○ Timers or stopwatches to ensure accurate intervention durations and sample collection intervals.
 
○ A calibrated pH meter to measure salivary pH.
 
○ Eppendorf tubes (3ml) for saliva collection, suitable for accommodating the electrode of the pH meter and ensuring accurate measurements.
 
 
 
 
Monitoring and Compliance:
To respect participants' privacy, researchers will not remain present during the kiss. However, they will ensure the proper initiation of the intervention and verify compliance with the protocol. Saliva collection and pH measurement will be monitored closely to ensure adherence to the timeline.
 
Justification of the Intervention:
The kiss was chosen as the intervention due to its widespread and accessible nature. Demonstrating that kissing can act as a protective factor against the reduction of salivary pH—and potentially against dental caries—could contribute positively to preventive strategies for oral health. The study aims to explore the physiological impact of kissing in a controlled and measurable manner.
 
Materials and Equipment Used:
 
 
1. Eppendorf tubes (3ml): These will collect unstimulated saliva and accommodate the pH meter electrode, as only minimal saliva is expected per sample.
 
2. Calibrated pH meter: This device will measure salivary pH with precision.
 
3. Screens (biombos): To ensure the privacy and comfort of participants during the intervention.
 
4. Timers/Stopwatches: To accurately measure the duration of the kiss and sample collection intervals.
 
 
Safety and Monitoring Measures:
The intervention (kissing) is considered a safe and low-risk activity, especially as it will involve habitual partners. The clinic, located within the university, operates with official permits and adheres to national and international standards for disinfection and biosecurity. The privacy provided by screens further enhances participant comfort. In the unlikely event of an unforeseen incident, the university's medical department will be on standby to provide immediate assistance.
 |

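### Section 11a sends kissing participants out of the cubicle for the post-kiss sample but keeps controls seated inside it, so place and movement at that sample depend on group

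*Protocol*

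**What the plan says.** Three parts of the Protocol bear on where and how the saliva samples are given.

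- **Section 11a, kissing groups.** Under Setting, after the kiss "participants will leave the cubicle to provide an unstimulated saliva sample". Under Implementation Standards, once the 40-second timer ends, "participants will be asked to leave the cubicle and provide their saliva sample".
- **Section 11a, Control Group.** "The individual who consumes the acidic beverage will remain in the same cubicle for 40 minutes, providing unstimulated saliva samples every 5 minutes". A closing clause in that sentence refers to what is required of the experimental groups. The next sentence adds: "The control participants will remain seated and follow the same sample collection timeline as the intervention groups". The section also has controls bring their partners so that conditions are alike across groups.
- **Section 9, Study setting.** "Saliva samples will be collected and pH measurements will be performed in the same private setting immediately following the intervention". No distinction is made between groups.

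Section 12 gives one measurement timeline for everyone: a baseline sample, a sample straight after the drink, then a kiss or a wait, then samples at 5-minute intervals for 40 minutes, nine post-intervention samples in all. Section 11c says samples are timestamped to check the intervals.

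**The concern.** In section 12 the only difference between groups after the drink is that some kiss and the others wait. Section 11a adds a second difference, because kissing participants get up and leave the cubicle to give a sample while controls stay in their seats. This follows from the assignment itself, so randomisation cannot balance it. No analysis can separate it from the kiss, because it is present in both kissing groups and absent in the control group.

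The protocol treats conditions at sampling as relevant to the outcome. It insists on unstimulated saliva because increased flow alters pH (section 12), and it withholds the assignment until the day of the session to avoid anticipatory salivation (sections 16b and 17a). A difference in place and movement tied to group does not fit with that care. There is also a practical problem: staff who read section 9 and staff who read section 11a could run the sampling differently.

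**Working it through.** No arithmetic decides this point, and the protocol gives no figure to reproduce. The check is to set the provisions side by side.

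| Feature at sampling | Kissing groups | Control group | Source |
|---|---|---|---|
| Place, first post-kiss sample | Outside the cubicle | Inside the cubicle | 11a |
| Place, later 5-minute samples | Not stated | Inside the cubicle | 11a |
| Movement before the first sample | Gets up and leaves | Stays seated | 11a |
| Nominal sampling times | Common schedule | Common schedule | 11a, 12 |
| Setting for collection and measurement | One private setting | One private setting | 9 |

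**Step 1: is there a sample to which the exit applies?** Yes. Section 12 has 5-minute intervals over 40 minutes, so 40 / 5 = 8 intervals, and it counts nine post-intervention samples. The ninth must therefore fall at the start: 8 + 1 = 9. Section 18a and Figure 1 also list a measurement immediately after the intervention. That is the sample for which section 11a sends kissing participants out.

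**Step 2: how many samples are affected?** At least one of nine. The number could be as high as nine if kissing participants stay outside afterwards, but the protocol does not say so. The closing clause of the control sentence can be read in two ways. It may carry over only the 5-minute schedule, or it may also carry over the stay in the cubicle. On the second reading the kissing participants return, and the difference is limited to a brief exit.

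**Step 3: does the timing differ?** Not on paper. Sections 11a and 12 give a common timeline, and section 11c provides timestamps. Section 12 has controls wait while the others kiss, but it gives the wait no length of its own and does not say from which moment the 5-minute marks are counted.

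**Step 4: can sections 9 and 11a both be followed?** Only if the single setting in section 9 means the wider private area and not the screened cubicle. Even on that reading, the kissing groups get up and move within the area and the controls do not.

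**Step 5: size.** The protocol has no data on the effect of place, movement or posture on salivary pH, so neither the size nor the direction of an effect can be derived.

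**The case against.** The strongest reply is that this is loose wording without a shown consequence. The exit is stated only for the sample right after the kiss. The space is reserved for the study on collection days, so stepping out of a screened cubicle need not mean leaving the private setting of section 9. Much of the protection is already planned: a common timeline, timestamps, coded tubes (Appendix 2) and control partners in attendance. Nothing in the protocol suggests that a few steps would change the pH of expectorated saliva enough to shift a recovery time read at 5-minute marks.

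Most of this stands, and it limits what can be claimed. A reader might infer four stronger things, none of which the text supports:

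- **A handling difference through all 40 minutes.** The place of the later samples in the kissing groups is left open.
- **A later first sample in the kissing groups.** The stated timeline is common to all groups.
- **More talking in one group.** No rule on talking differs by group.
- **Loss of masking caused by the place of sampling.** An investigator already watches the kiss begin and starts the timer (sections 11a and 11c), so the place reveals little more. How that fits with the masking of data collectors in section 17a is a separate question.

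The objection does not remove the instruction itself. It appears twice in section 11a, applies only to those who kiss, and has a seated, in-cubicle counterpart for the controls.

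**Conclusion.** The point holds in a limited form. As section 11a is written, place and movement depend on group at least at the first post-kiss sample, and section 9 describes one setting for all. This is an avoidable handling difference and an unclear instruction. It is not a demonstrated bias.

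The certain extent is one of nine post-intervention samples, in both kissing groups and in no control. Any effect on pH cannot be quantified from the protocol and is probably small; that last judgement is an assumption. The conclusion also takes the two statements in section 11a about leaving the cubicle as instructions to be carried out. It does not depend on how the clause closing the control sentence is read. The point is minor, but worth acting on because uniform handling costs so little.

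**What to change.** Reconcile sections 9 and 11a (Setting, Control Group and Implementation Standards) so that one rule covers all three groups:

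- Every sample is given in the same place, with the participant seated.
- The common time points are counted from the end of the kiss or, for controls, from the end of a wait of equal length. Section 11a gives 40 seconds for the kiss while section 6b gives 2 minutes; those passages need reconciling separately, and the wait should match whatever is settled.
- The place of the later 5-minute samples is stated explicitly for the kissing groups.
- The tubes, which already carry codes, are read at the pH meter by a team member who did not supervise the kiss.

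The cost is a change of wording, a change of where participants sit and a division of tasks within the existing team. No extra equipment or samples are needed. Section 2b lists the trial as not yet recruiting, so on that status the change can be in place before the first session; section 25 would route it through the ethics committee as an amendment.
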